## Abstract

**Background:**

Smoking cessation interventions implemented in emergency department (ED) settings have resulted in limited success, owing to factors such as lack of time, motivation, and incentives. A dynamic yet simple and effective approach that addresses the fast-paced nature of acute-care ED settings is needed. This study proposes a multi-center randomized controlled trial (RCT) to compare the effectiveness of an easy to deliver proactive, multi-component tobacco treatment intervention to usual care in the ED setting.

**Methods:**

This will be a prospective four-site, single-blind, blinded-endpoint (PROBE) RCT. Participants will be recruited directly in the ED and will be approached strictly in order of arrival time. Those randomized to the Quit Card Intervention (QCI) group will receive a “quit kit” which will include: a “Quit Card” worth $300 that can be used at any Canadian pharmacy to purchase any form of nicotine replacement therapy (NRT); a self-help booklet; and proactive enrolment in 6 months of telephone follow-up counseling. The usual care (UC) group will receive a “quit kit” which will include a brochure for a local smoking cessation program. Quit kits for both groups will be delivered in opaque, sealed envelopes, and identical in size and weight so to conceal group allocation from the blinded research coordinator. Randomization will be stratified by site and by the Canadian Triage Acuity Scale (CTAS), a value assigned to each ED patient based on the severity of the condition. An equal number of quit kits will be prepared for each CTAS level. The primary outcome will be bio-chemically verified smoking abstinence at 26 weeks. Secondary outcomes include smoking behavior at weeks 4, 52, and 104 as well as mortality and health care utilization outcomes. Investigators, outcome assessors, and data analysts will be blinded to group allocation until after primary analyses are completed. It is hypothesized that the QCI group will have higher a abstinence rate, improved health outcomes, and decreased healthcare utilization.

**Discussion:**

There are few examples of hospital EDs in Canada that systematically initiate tobacco cessation interventions for patients who smoke. Given the high smoking prevalence among ED patients and the relation of tobacco smoking to the majority of ambulatory care sensitive conditions, EDs are a missed opportunity in the initiation of tobacco treatment interventions. We have designed and will test an evidence-based tobacco treatment intervention that is simple and highly scalable.

**Trial registration:**

ClinicalTrials.govNCT04163081. Registered on November 14, 2019

## Administrative information

Note: the numbers in curly brackets in this protocol refer to SPIRIT checklist item numbers. The order of the items has been modified to group similar items (see http://www.equator-network.org/reporting-guidelines/spirit-2013-statement-defining-standard-protocol-items-for-clinical-trials/).

## Introduction

### Background and rationale {6a}

#### Background

In Canada, smoking results in nearly 40,000 premature deaths per year and it has been estimated that smoking-attributable healthcare use will cost approximately $80 billion over the next 20 years [1]. Heart disease and stroke are 2–4 times more common among smokers compared to non-smokers, and smoking accounts for 80–90% of all chronic obstructive pulmonary disease cases and 30% of all cancer deaths [2, 3]. Individuals who smoke have a 30–40% greater chance of developing type II diabetes, and those with diabetes have a greater risk of morbidity and premature mortality [4, 5]. Smokers use twice as many hospital days annually and are being hospitalized, on average, 12 years earlier than their non-smoking counterparts [6, 7].

Smoking cessation results in improvements in vascular, respiratory, and cancer-related health outcomes [3, 8], and reduces the prevalence and incidence of vascular events (e.g., acute myocardial infarction, stroke) substantially within the first few years [9, 10]. If a person quits before the age of 40, they will eliminate 90% of their risk of premature morbidity and mortality associated with smoking [8]. Hospital-initiated cessation interventions have been found to decrease 30-day, 1-year, and 2-year re-hospitalization rates, thus indicating the potential for improving “avoidable” hospital readmissions [6]. Despite progress in reducing the current smoking prevalence in Canada to 13%, there is a need for increased cessation efforts in order to reach Canada’s goal of 5% prevalence by 2035 [11]. Wider-scale implementation of proactive interventions initiated in clinical environments that treat large volumes of smokers is needed.

#### Rationale

Given the high smoking prevalence among patients treated in emergency departments (ED) [12], ED settings are an opportune and critical target area to initiate tobacco treatment and aftercare. Smoking rates among ED patients have been found to be >5% higher than levels in the general population [13, 14]. In a pilot study completed by our research team, an assessment of smoking prevalence completed at four hospital sites to be included in this study revealed that 509 of 2713 (19%) of patients reported current smoking. Therefore, the ED is an ideal environment to reach smokers and initiate tobacco treatment. However, few EDs in Canada offer tobacco treatment interventions to patients due to the environment’s fast-paced and acute care nature. Interventions in the ED must be simple and fast to deliver to facilitate implementation among ED staff.

Previous cessation intervention trials in ED settings have mostly found non-significant differences in abstinence rates (from −3.6 to 20%) between intervention and control groups [15]. Limitations of previous studies have included (1) low intensity of interventions (e.g., brief advice initiated in the ED and passive referral to a telephone “quit line”); (2) single-site studies, limiting generalizability; (3) weak-to-moderate methodological quality of most (88%); and (4) lack of health services outcomes (e.g., mortality, healthcare use, cost). Motivational interviewing (MI)-based counseling for smokers in the ED has shown to be effective; however, it has been acknowledged that, due to time constraints present in the ED, briefer interventions may be better suited for this setting [15]. A Canadian RCT compared advice from an ED physician and referral to a quit line to usual care (no support) [16]. In total, 660 patients were randomized to the intervention group, of whom 412 agreed to a quit line referral. Of those, only 13% enrolled in the quit line intervention, and only ~5% completed the program. Not surprisingly, given the low uptake, no significant differences in cessation were found between groups.

Clinical tobacco treatment interventions that include medication and behavioral counseling are most effective at helping people quit smoking [17]. NRT is the most frequently used cessation medication in acute care settings given its rapid effect on nicotine withdrawal. A systematic review and meta-analysis examining the effect of NRT reported an odds ratio (OR) of 1.84 (95% confidence interval (CI) 1.71–1.99)) for long-term cessation when comparing NRT to placebo. Combination NRT (e.g., pairing a nicotine patch with a shorter-acting form like gum, inhaler, or mouth spray) is more effective than nicotine monotherapy (OR 1.34, 95% CI 1.00–1.8) [18]. Behavioral counseling is crucial in supporting cessation efforts and preventing relapse. Proactive enrolment in behavioral support programs, as opposed to passive referral, is necessary. A recent study of a smoking cessation intervention in an out-patient surgery clinic found that 85% of patients enrolled in smoking cessation counseling when an “opt-out” referral approach was implemented [19]. This is compared to a 23% enrolment rate observed when hospitalized patients were referred to the same program using “opt-in” approaches [20]. A 2013 systematic review and meta-analysis of telephone counseling trials found positive effects for interventions involving multiple sessions of proactive counseling compared with self-help or single-session brief counseling (relative risk [RR] 1.41, 95% CI 1.20–1.66) [21].

### Objectives {7}

The main objectives of the INITIATE study are to determine whether, compared to usual care, smokers visiting an ED who receive a proactive tobacco treatment intervention initiated with a “Quit Card”:
Will be more likely to quit smoking over the long term (≥6 months);Will have reduced rates of healthcare utilization and death (from 30 days to ≥ 2 years)?

### Trial design {8}

This trial is a prospective, multi-site, randomized, single-blind, blinded-endpoint (PROBE) trial. Consenting participants will be randomized 1:1 to receiving usual care (UC, control group) versus the Quit Card-initiated intervention (QCI, treatment group). (See Fig. 1).

**Fig. 1 Fig1:**
[figure not shown]
Flow diagram of INITIATE trial

## Methods: participants, interventions, and outcomes

### Study setting {9}

We anticipate recruiting patients presenting to the ED at four hospitals which do not currently offer cessation support to ED patients and have >35,000 ED visits per year. The two primary recruitment sites will be two campuses of The Ottawa Hospital (TOH), an academic health sciences center located in Ottawa, Ontario. Additionally, participants will be recruited from Hôpital Montfort (urban) and Winchester District Memorial Hospital (rural community hospital).

### Eligibility criteria {10}

Participant inclusion criteria are the following:
Current daily smokers (smoke ≥ 5 cigarettes per day)≥ 18 years of age (the age of majority in Ontario)Assigned a Canadian Triage and Acuity Scale (CTAS) level of 2–5 (emergent to non-urgent)Able to read and understand English or FrenchResides in Ontario and eligible for Ontario Health Insurance Plan (to permit linkage with administrative data housed at the Institute for Clinical Evaluative Sciences [ICES])Available and willing to participate in follow-up assessments over the next 24 monthsHas access to a telephone or computerAble to provide informed consent.

Exclusion criteria are the following:
Currently participating in this or another smoking cessation studyAssigned a CTAS level of 1 (resuscitation—the most seriously ill patients with the highest likelihood of hospital admission) or in a psychiatric emergency unitPregnant, planning to become pregnant over the next 2 years, or breastfeedingHas morbid illness which will prevent completion of 26-week follow-up (e.g., receiving palliative care)In the ED physician’s opinion, manifests acute physical and/or psychiatric illness or has a cognitive impairment that would preclude participation in/benefit from the intervention.

### Who will take informed consent? {26a}

The research coordinator (RC) will be responsible for the recruitment of study participants and obtaining informed consent.

### Additional consent provisions for the collection and use of participant data and biological specimens {26b}

Additional consent will be obtained to link data to select healthcare administrative databases to evaluate health and health services outcomes. For consenting participants, study data will be individually linked to healthcare administrative databases at the Institute for Clinical Evaluative Sciences (IC/ES) using their unique Ontario Health Insurance Plan (OHIP) number.

### Intervention description {11a}

#### Usual care (UC) group

UC will be standardized across participating EDs. Eligible consenting participants randomized to the UC group will receive a kit that contains a brochure for the University of Ottawa Heart Institute’s Quit Smoking Program (QSP), a 6-month nurse-led behavioral counseling program. The brochure will include a description of the QSP program and information about how to register. UC participants will be able to self-register in the program if they so choose.

#### “Quit Card” intervention (QCI) group

Eligible consenting participants randomized to the QCI group will receive a kit that contains a “Quit Card” worth $300 that they can take to any pharmacy to purchase any type and brand of NRT (an approximate 6- to 12-week supply of combination NRT), and they will also receive proactive, tailored behavioral support from a study counselor for 26 weeks. QCI participants will have up to 2 months from study entry to use the full value of their Quit Card to encourage quit attempts. If a participant’s Quit Card expires before they use the full value and they would like to continue NRT, it will be possible for the study counselor to extend the expiration date. The study counselor will call QCI participants within the first week of study entry to initiate the behavioral support. Participants will receive at least four additional proactive (live) counseling calls, plus three automated calls or emails (based on participant preference) over 6 months (Table 1). During the counseling calls, the counselor will use standard follow-up protocols based on established baseline treatment goals [17]. The automated messages will be motivational and will include tips and reminders of what number to call should a participant wish to speak with the counselor for support [27].

**Table 1 Tab1:** Behavioral support schedule

	Days after study enrolment						
	Days 3–7	Day 14	Day 45	Day 60	Day 90	Day 120	Day 150
Live call	X	X	X		X		
Automated call or email				X		X	X

#### Criteria for discontinuing or modifying allocated interventions {11b}

If a participant chooses to withdraw from the intervention, the intervention will stop at the moment of the participant’s request. If a participant consents to the use of their data, all data obtained up to that point of the request will be retained and utilized for subsequent data analysis in the duration of the trial.

The proposed intervention of the use of NRT for participants allocated to the QCI group is considered low risk. A systematic review and meta-analysis (92 RCTs, 28 observational trials) reported NRT patch-use was associated with increased skin irritation (OR 2.80, 95% CI, 2.28–3.24) and oral NRTs associated with mouth and throat soreness (OR 1.87, 95% CI, 1.36–2.57), mouth ulcers (OR 1.49, 95% CI, 1.05–2.20), hiccups (OR 7.68, 95% CI, 4.59–12.85), and coughing (OR 2.89, 95% CI, 1.92–4.33) [28]. A network meta-analysis (21 RCTs) found no evidence of increased risk of serious cardiovascular events with NRT (RR 1.95, 95% CI 0.26–4.30); however, it did report an elevated risk, mostly due to less serious events such as heart palpitations (RR 2.29, 95% CI 1.39–3.82) [29]. These reported risks are irrefutably much lower than those associated with continued smoking. If prolonged side effects are seen, NRT products used by participants allocated to the QCI treatment group may be modified.

#### Strategies to improve adherence to interventions {11c}

The behavioral counseling schedule has been designed to contact patients at important time points in terms of relapse prevention and Quit Card redemption reminders.

#### Relevant concomitant care permitted or prohibited during the trial {11d}

The use of other smoking cessation aids (e.g., varenicline, bupropion, vape devices) or participation in other smoking cessation interventions or programs will be queried during follow-up assessments and controlled for.

#### Provisions for post-trial care {30}

Upon request, study participants from either allocated group may be eligible for smoking cessation support post-trial.

#### Outcomes {12}

##### Primary outcome

The primary outcome will be smoking abstinence at 26 weeks, biochemically verified using an expired CO test.

##### Secondary outcome

Secondary outcomes related to smoking behavior include the following:
Prolonged (since last follow-up assessment) abstinence, at 4, 26, 52, and 104 weeksPoint prevalence abstinence at 4, 52, and 104 weeksSmoking reduction (i.e., change in the number of daily cigarettes) at 4, 26, 52, and 104 weeksNumber of quit attempts since study entry at 4, 26, 52, and 104 weeksUse of cessation medication and/or e-cigarettes at 4, 26, 52, and 104 weeksUse of behavioral supports (e.g., counseling, quit lines) at 4, 26, 52, and 104 weeksHealth-related quality of life (HR-QoL) at 52 and 104 weeks

Secondary outcomes related to health services include the following:
All-cause and smoking-related (e.g., vascular, respiratory, cancer-related) visits to ED, admissions to hospital, and mortality at 4, 26, 52, and 104 weeksCost-effectiveness ratios at 52 and 104 weeks

#### Participant timeline {13}

Please see Fig. 2.

**Fig. 2 Fig2:**
[figure not shown]
Schedule of recruitment, interventions, and assessments

#### Sample size {14}

The primary outcome of smoking abstinence at 26 weeks was used to calculate the sample size (PASS 16.0.2, www.ncss.com). Using logistic regression, with 905 participants assigned in a 1:1 allocation to the two groups, we will have 80% power to detect a clinically important 5% difference in smoking abstinence rates between the QCI and UC groups and >90% power to detect a 10% difference (two-sided test; alpha = 0.05). While we have included features to minimize attrition, we have increased our sample to account for a 25% loss to follow-up [30]; therefore, we intend to recruit 1208 participants to allow for per-protocol analyses.

In our assessment of intervention effect on health services, using a two-sided log-rank test and accounting for the competing risk of death, with 1208 participants we will have >90% power to detect a hazard ratio of 0.63 for all-cause re-hospitalization and 77% power to detect a hazard ratio of 0.82 for visits to the ED over 2 years (25% loss to follow-up; alpha = 0.05). We will have >90% power to detect a hazard ratio of 0.45 for death. This assumes cumulative incidence proportions for hospitalization of 0.45 for the UC group and 0.34 for the QCI group, ED visits of 0.68 for UC and 0.66 for QCI, and death of 0.15 for UC and 0.07 for QCI, based on a trial of hospitalized smokers conducted by our group [6].

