### Statistical methods

#### Statistical methods for primary and secondary outcomes {20a}

For our primary analysis of the effect of the intervention on smoking abstinence, we will use binary logistic regression. We will complete unadjusted and adjusted models testing for site-by-treatment interactions and assessing the clinically important predictors of level of nicotine dependence and education.

For our analysis of intervention effect on clinical events, we will use competing-risk regression [33]. Competing-risk regression compares the cumulative incidence of an event (i.e., hospitalization, ED visit) between two groups over a period of time in the presence of a competing risk (i.e., death). The primary independent variable in our models will be group (QCI vs. UC group).

We will also assess the effect of quitting on clinical outcomes, using smoking status as the independent variable in our models. An alpha level of 0.05 and two-tails will be used for all tests of significance and interval estimates will be based on 95% confidence intervals. We will use intention-to-treat principles and the Russell standard (the convention in cessation trials), removing patients who have deceased or become untraceable (e.g., number no longer in service, moved with no forwarding address or number) and assuming that those lost to follow-up (e.g., those who refuse contact) are smoking [34]. We will conduct per-protocol analyses using “engaged” participants (all who used their Quit Card and/or partook in ≥1 behavioral support contact). Analyses will be carried out using statistical software packages SAS (Cary, NC) and SPSS.

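### The 77% power for ED visits belongs to a cause-specific log-rank test; at the plan's own rates, the planned cumulative-incidence analysis has about 11% to 25%

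*Protocol article*

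**What the plan says.** Sample size {14} in the protocol article derives the health-services power "using a two-sided log-rank test and accounting for the competing risk of death, with 1208 participants", under "25% loss to follow-up; alpha = 0.05". For ED visits it reports "77% power to detect a hazard ratio of 0.82 for visits to the ED over 2 years". The planning incidences behind this include "ED visits of 0.68 for UC and 0.66 for QCI, and death of 0.15 for UC and 0.07 for QCI". For hospitalization they are 0.45 and 0.34, with a hazard ratio of 0.63.

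Statistical methods for primary and secondary outcomes {20a} says clinical events will be analysed by competing-risk regression, and explains what that means: "Competing-risk regression compares the cumulative incidence of an event (i.e., hospitalization, ED visit) between two groups over a period of time", with death as the competing risk.

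**The concern.** Where death competes with the event of interest, two different hazard ratios can be formed. The cause-specific hazard ratio compares event rates among people still alive and event-free. The subdistribution hazard ratio corresponds to the cumulative incidence, that is, the proportion who ever have the event by a given time. If the arms differ sharply in death, the two can lie far apart.

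The ED-visit rates differ by only 2 percentage points over two years, while assumed death falls by more than half. A hazard ratio of 0.82 is hard to square with 0.68 vs 0.66 on the cumulative-incidence scale, which is the scale that {20a} says will be compared. If the power was computed on the other scale, it does not describe the planned analysis. Reduced healthcare use and death is the second of the two main objectives (Objectives {7}), so a non-significant ED result could then be judged against a power claim that the analysis never had.

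**Working it through.** **Inputs.** N = 1208 ("we intend to recruit 1208 participants"); 1:1 allocation ("Consenting participants will be randomized 1:1"), so 604 per arm; 25% loss and two-sided alpha 0.05; the two-year incidences in Sample size {14}. Two years is taken as one time unit.

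**Step 1: reproduce the stated hazard ratios.** Assume constant cause-specific hazards, with F the event incidence and D the incidence of death as the competing event. Then h = −ln(1 − F − D) × F/(F + D).

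- ED visits, UC: −ln(0.17) × 0.68/0.83 = 1.452
- ED visits, QCI: −ln(0.27) × 0.66/0.73 = 1.184
- Ratio: 1.184/1.452 = 0.815 (stated 0.82)
- Hospitalization: 0.4375/0.687 = 0.637 (stated 0.63)
- Death, with no competing event: ln(0.93)/ln(0.85) = 0.447 (stated 0.45)

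**Step 2: reproduce the 77%.** Take exponential loss with hazard −ln(0.75) = 0.288. The proportion with an observed ED visit is h/t × (1 − e^−t), where t is the sum of the event, death and loss hazards. This is 0.615 in UC and 0.591 in QCI, so 604 × (0.615 + 0.591) gives about 728 events. The Schoenfeld formula is power = Φ(√events/2 × |ln HR| − 1.96).

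- HR 0.815: Φ(2.754 − 1.96) = 78.6%
- HR 0.82: Φ(2.678 − 1.96) = 76.4%

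The stated 77% lies between them. Treating the loss as half exposure (about 708 events) gives 77.5% and 75.2%.

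**Step 3: where the 0.82 comes from.** The log hazard ratio is ln(0.815) = −0.204.

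- Death equal at 0.15 in both arms, ED 0.68 vs 0.66: HR 0.932, which is 34% of the log hazard ratio
- Death equal at 0.07 in both arms: HR 0.942, which is 29%
- ED equal at 0.68 in both arms, death 0.15 vs 0.07: HR 0.866, which is 71%; power would be about 49% with no difference in the proportion visiting the ED

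The ED difference therefore supplies about 30% to one-third, and the assumed fall in death the rest.

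**Step 4: power for the planned comparison.**

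- Proportional subdistribution hazards: HR = ln(1 − 0.66)/ln(1 − 0.68) = ln(0.34)/ln(0.32) = 0.947. With 728 events, Φ(0.738 − 1.96) = 11.1%; with 809 events (no loss), 11.9%.
- Two proportions at two years, 604 per arm: 11.1%.
- Simulation under the constant cause-specific hazards of Step 1 (4000 trials, 604 per arm, 25% exponential loss), using a Gray / Fine-Gray-type test: 24.6%, with an average subdistribution hazard ratio of about 0.91. In the same simulated data the cause-specific log-rank test had 79.3%.

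If N is first cut to 906 for loss, the range is about 9% to 21%.

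**Step 5: the other two figures.**

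- Hospitalization: subdistribution HR = ln(0.66)/ln(0.55) = 0.695. With 1208 × 0.395 = 477 events the power is about 98%; with N = 906 it is about 93%.
- Death at HR 0.447: with 1208 × 0.11 = 133 events the power is 99.6%; with N = 906 it is 98%.

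**The case against.** The 77% is right for the test that Sample size {14} names, so this is not an arithmetic slip. That is correct: the defect is a mismatch between two sections. ED visits are also a secondary outcome, the trial is sized on 26-week abstinence, and {20a} already commits to 95% confidence intervals. All of that stands and limits the severity.

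Three stronger readings are tempting but not supported.

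- A reader might infer that the health-services power fails throughout. It does not: hospitalization and death both keep more than 90% at the plan's own rates, and the scale mismatch does not touch death, which is itself the competing event.
- A reader might infer that nearly all of the 0.82 is a mortality effect. Step 3 puts that share at about two-thirds to 70%.
- A reader might go on to say that "power to detect a hazard ratio of 0.45 for death" is implausible, because a modest gain in abstinence could not produce such a fall in death. The documents do not settle this. They give no baseline abstinence rate for the sample size. The 5-point gap is a difference to detect, not a forecast. Smoking reduction is also listed as an outcome, so abstinence need not be the only pathway. The rates are attributed to an earlier trial that is not available here.

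**Conclusion.** The stated ED-visit power is not a property of the analysis that {20a} describes. At the plan's own rates, the cumulative-incidence comparison has about 11% to 25% power at N = 1208, against the 77% stated.

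The lower end assumes proportional subdistribution hazards, or a comparison of proportions at two years. The upper end assumes constant cause-specific hazards and counts every planning death as occurring before any ED visit; the protocol states neither. The second assumption also supports the 77% itself. If only half the deaths in each arm came before a first ED visit (0.075 vs 0.035), the cause-specific hazard ratio would be 0.89 and, with 728 events, its power about 35%. No approach tried brings the planned comparison near 77%.

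Severity is moderate: one figure, for one secondary outcome, in a domain that the protocol lists as a main objective.

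**What to change.** Choose one of two routes.

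1. Keep the cumulative-incidence analysis. In Sample size {14}, give its ED-visit power (about 11% to 25%, with the assumptions behind each end) and label the 77% at hazard ratio 0.82 as a cause-specific log-rank figure.
2. Keep the 77%. In {20a}, name the cause-specific hazard as the target for ED visits, and report it beside cumulative incidence and mortality so that a change in death is not read as a change in ED use.

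The power statements for hospitalization and death need no change on this account. The cost is wording and, under the first route, a less favourable power figure; no extra participants or data are needed.
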